**Figure 1 f1:**
[figure not shown]
Overview of study procedure..

Participants are community-dwelling older adults, both men and women, aged 60 years or older who meet Petersen criteria will be included (31). Participants who meet the following criteria will be allowed to withdraw from this program, having severe medical events that occurred during the training or follow-up period, and should not continue to receive this program, reluctant themselves in training at any time, and a major protocol violation. Detailed inclusion and exclusion criteria are listed in **Table 1**. This study will be carried out following the recommendations of SPIRIT Guidelines with written informed consent from all participants who meet inclusion criteria or their surrogate family members. Ethical approval was approved by the Medical Ethics Committee of the Third People’s Huzhou Hospital of Zhejiang Province (number 2018-030).

**Table 1 T1:** Inclusion and exclusion criteria.

Inclusion criteria	Exclusion criteria
Fulfils the diagnostic criteria of MCI proposed by Petersen (31) Subjective or informant-reported of memory or cognitive decline/complaints Objective memory impairment (or other cognitive functions) inconsistent with age and educational background evaluated by age-adjusted scores at least 1.5 SDs below the mean on the Logical Memory subtest of Chinese version of the Wechsler Memory Scale-Revised (WMS-R) Preserved global cognitive function (MMSE ≥ 24; MoCA <26 when education level >12 years or MoCA <25 when education level≤12 years) Intact activities of daily living Do not meet dementia criteria. Aged 60 years or older Have at least primary school education (>5 years) No significant visual and hearing impairment and color blindness Willingness to participate in entirety of study Capacity to provide written informed consent	History of presence of a neurocognitive disorders (e.g. epilepsy, Parkinson’s disease, head trauma, stroke, mental retardation) and serious medical conditions that can cause brain dysfunction. Take cognitive enhancers, antidepressants in the last month History of presence of severe psychiatric disorders. (e.g., severe depression, active suicidal ideation, anxiety, schizophrenia and alcoholism and drug abuse); Participants in another training related to cognitive function or any investigational drug study at the same time

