#### Statistical Considerations

The primary and secondary outcome measures were analyzed using data from the intention-to-treat. Moreover, the protocol set principle was defined as those participants or the participants who completed at least 80% adherence to the program initially formulated and assessments all the required will be included. We will compare the characteristics of the completed participants versus dropout ones. Sensitivity analyses of completed participants will be further performed to explore the potential for dropout participants, and the results will be categorized as bias. Listwise deletion will be adopted to estimate treatment effects and sensitivity of the cluster dropout if missing values satisfy the criteria of the losing data entirely at random; otherwise, multiple imputation data strategies will be adopted.

Data processing and statistical analysis will be conducted using SPSS 21.0 and MatLab (The Mathworks Inc. 2016). Descriptive statistics will be reported as frequencies for categorical variables and means ± standard deviations for continuous variables. The adoption mainly the method of exploratory analysis to examine the distribution state of data. The proportionality of baseline data for both groups is compared by the non-parameters Wilcoxon test, chi-square test, and t-test. Regarding the primary outcome, a repeated ANOVA test will be used to evaluate the differences of changes and long-term effect in outcome measurement index performance in the cognitive training group and the wait-list control group, within-group over time, and interaction effects. The simple effect analysis will be added when there is an interaction between intervention factors and time factors. Secondary outcomes will be analyzed using similar statistical methods. The mediating effect model was used to test the transfer effect of cognitive training on untrained cognitive domains, with cognitive training as the mediator. A significant statistical will be considered as P < 0.05 for all comparisons. The effect size (r) was calculated using Cohen’s d to estimate the between-group effect sizes.

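### If data are judged missing completely at random, the completer check on dropout repeats the main analysis; in neither missing-data branch does it test dropouts doing worse than similar participants who stay

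*Protocol article*

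**What the plan says.** The relevant text is in the first paragraph of Statistical Considerations in the protocol article.

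- **Main analysis set:** "The primary and secondary outcome measures were analyzed using data from the intention-to-treat".
- **A second set**, restricted to those who "completed at least 80% adherence to the program initially formulated and assessments all the required will be included".
- **A descriptive check on dropout:** "We will compare the characteristics of the completed participants versus dropout ones".
- **An outcome check on dropout:** "Sensitivity analyses of completed participants will be further performed to explore the potential for dropout participants, and the results will be categorized as bias".
- **A missing-data rule with two branches.** If the data are judged missing completely at random, "Listwise deletion will be adopted to estimate treatment effects and sensitivity of the cluster dropout". If not, "otherwise, multiple imputation data strategies will be adopted".

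The next paragraph gives the primary model: "a repeated ANOVA test will be used to evaluate the differences of changes and long-term effect". Study Procedure and Table 3 put the assessments at baseline, 10 weeks and 3-month follow-up.

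Study Design and Participants lists the grounds for withdrawal: severe medical events during training or follow-up, and also "reluctant themselves in training at any time, and a major protocol violation".

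**The concern.** A sensitivity analysis for dropout should change what is assumed about the people who left and show whether the conclusion survives. The analysis named here looks only at people who stayed.

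In the listwise branch the main analysis has already removed everyone with a missing visit, so the check returns the main result and cannot fail. In the imputation branch the check rests on a stronger assumption (missing completely at random) than the one multiple imputation ordinarily makes (missing at random). It can show that observed predictors of dropout matter. It cannot show what happens if dropouts fared worse than their observed data predict.

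That last possibility is realistic here. Medical events and reluctance to train can both relate to cognitive outcome, and only one arm is offered the cognitive training before outcome assessment is complete. A favourable result could be reported as robust to withdrawal on the strength of a check that never tested it.

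**Working it through.** **Inputs**

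- From the sample-size paragraph: dropout 15%, 46 per group (92 in total), 78 before dropout, standardised effect 0.575.
- From Statistical Considerations: the two-branch missing-data rule and the repeated-measures ANOVA.
- Assumed, not in the documents: the shortfall of dropouts (0 to 1 SD), and the simulation settings given in step 5.

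**1. The plan's own dropout figure.** 78 / (1 − 0.15) = 91.8, rounded up to 92, which reproduces. Expected dropouts are 0.15 × 92 = 13.8, about 14. The Abstract's total of 90 gives 0.15 × 90 = 13.5, which is practically the same.

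**2. Listwise branch.** A repeated-measures ANOVA over three visits with listwise deletion keeps participants with all three visits. A completer analysis, read as participants with all assessments, keeps the same people. Same rows and same model give the same estimate and a difference of exactly 0. The plan's wording supports this, since it applies listwise deletion both to the treatment effect and to the dropout sensitivity. The 80%-adherence set also requires every assessment, so in this branch none of the outcome analyses named includes a dropout.

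**3. How firmly the branch can be chosen.** Whether data are missing completely at random cannot be verified from the data; only dependence on observed variables can be tested. With 14 dropouts against 78 completers, the standard error of a standardised baseline difference is √(1/14 + 1/78) = 0.29. The difference detectable with 80% power at two-sided 5% is about (1.96 + 0.84) × 0.29 = 0.81 SD (normal approximation). Smaller departures would often be missed and the listwise branch taken.

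**4. What an unobserved shortfall would do.** Let p be the dropout share and δ the shortfall of dropouts, in SD, against what the analysis assumes for them. The group difference falls by p(training) × δ(training) − p(control) × δ(control).

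| Assumed δ in training-arm dropouts (control 0) | Fall in group difference at 15% dropout | Share of 0.575 |
|---|---|---|
| 0 | 0 | 0% |
| 0.25 SD | 0.15 × 0.25 = 0.0375 | 6.5% |
| 0.5 SD | 0.15 × 0.5 = 0.075 | 13% |
| 1 SD | 0.15 × 1 = 0.15 | 26% |

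With the same δ and the same dropout rate in both arms, the fall is 0.15 × δ − 0.15 × δ = 0.

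**5. Simulation of the two branches.** Each scenario used 2,000 trials of 46 per arm, a true effect of 0.575 and a baseline-to-outcome correlation of 0.6. The estimate was the group difference in change at one post-baseline visit, a simplification of the three-visit model. In the second and third scenarios control dropout was 5% and training-arm dropout fell mainly among low scorers. Training-arm dropout was therefore 2 × 0.162 − 0.05 = 27%, more uneven than anything the protocol states.

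| Dropout depends on | Overall dropout | Listwise and completers | Imputation (missing at random) | Imputation, training-arm shift −0.8 SD |
|---|---|---|---|---|
| nothing | 15.0% | 0.568 | 0.567 | 0.449 |
| observed baseline | 16.2% | 0.460 | 0.581 | 0.361 |
| unobserved outcome | 16.2% | 0.700 | 0.778 | 0.559 |

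Listwise and completer estimates agree in every trial because they use the same rows. In the second row the gap between completers (0.460) and imputation (0.581) is informative, and imputation is close to the truth. In the third row both planned analyses are too high, and their gap (0.700 against 0.778) does not reveal it. Only the shifted imputation brings the estimate down: 0.778 − 0.274 × 0.8 = 0.559. The shift is an assumption to be varied; in the first two rows the same −0.8 SD over-corrects.

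**The case against.** **The imputation branch is informative.** A reader might infer that the check can never show whether withdrawals changed the result. The documents do not support that. Where imputation is used, the completer contrast does show the effect of dropout that depends on observed data (0.460 against 0.581 above). What stands is narrower: neither branch probes dropouts doing worse than similar participants who stay.

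**The listwise branch is conditional.** The plan reserves listwise deletion for data missing completely at random, where it does no harm. The criticism bites only if that judgement is wrong. This is fair, but a check on dropout is needed precisely because the judgement cannot be verified.

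**Completers are not defined.** Next to an 80%-adherence set, the term could mean people who finished training. That set could differ from the listwise one, and the results would then not be identical. The identity holds for the reading used here, participants with all assessments. The other reading still gives a selected set and is no better as a probe.

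**The bias sentence is unclear.** A reader might take it as a rule that any difference from completers is bias. The wording does not clearly say so and may only mean that the findings will be discussed under attrition bias. It needs rewording; it is not proof of a wrong rule.

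**Arms.** A reader might infer that completers and dropouts are compared with the arms pooled, so that arm-specific dropout would go unseen. The article does not say whether the comparison is pooled, and such detail is commonly left to the analysis plan.

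**Masking.** Calling the trial unmasked would be wrong: the Abstract says single-blinded, and Outcome Measurement says evaluators are blinded. Participants do know whether they are receiving training. Control participants also attend twice-weekly classes, so reluctance to continue can arise in both arms, which is why the illustrated range includes 0.

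**Condensed article.** Leaving out a particular imputation technique would not be an error. Here, however, the article names a specific analysis for a stated purpose, and that analysis cannot fully serve it.

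**Conclusion.** The point holds in limited form. In the listwise branch, reading completers as participants with all assessments, the dropout check duplicates the main analysis and shows a change of exactly 0 whatever the dropouts' outcomes were. In the imputation branch it informs about dropout related to observed data only. In neither branch does the article name an analysis that varies the assumption about unobserved outcomes, although its own withdrawal grounds make outcome-related dropout plausible.

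The possible size is 0 to 0.15 SD, or 0 to 26% of the planned effect of 0.575. This rests on the protocol's 15% dropout and on assumed shortfalls of 0 to 1 SD in the training arm alone; with equal shifts and dropout rates in both arms it is 0. The documents give no evidence on which value applies. They do not show that the result will be biased, only that the planned check would not settle the question.

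**What to change.** In Statistical Considerations:

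1. Base the dropout sensitivity analysis on multiple imputation of all randomised participants. Add a delta-adjusted (tipping-point) shift to the imputed 10-week values, for example 0 to 1 SD in steps, varied separately by arm. Report the shift at which the conclusion changes.
2. Keep the completer analysis as supportive only, and define completers.
3. Reword the sentence on bias so that a difference from the completer result is not itself labelled bias.

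Reporting the number, timing and reasons of dropout by arm would be a useful addition; it does not correct an error in the plan.

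The cost is a change of wording and a few hours of analysis, with no new data. The downside is that the reported robustness may look less favourable.

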The calculation of sample size is based on the change in executive function after 10-week, which is the primary outcome variable in this study. A meta-analysis found that significant benefits of cognitive training are superior to the wait-list and the effect size of executive function training used to calculate the sample size is 0.575 [0.093,1.056] (18, 19). Sample size estimation was conducted using statistical software G*power. In the analysis with an independent t-test using a power of 80% and a type 1 error of 5%, the calculated total sample for this study is 78. Considering a 15% dropout rate and maximum to ensure the credibility of the cognitive training, we will recruit 46 participants in each group. Thus, the total required sample size for this study is 92 participants.

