#### Study Procedure

Participants will be enrolled from the nearby community health service centre via open recruitment through paper flyers, online forums, and word-of-mouth. Participants who interested in this program will be invited for an in-person interview to complete a screening questionnaire in the community health service centre, including demographic characteristics, MMSE, MoCA, ADL, and Achromatopsia anomalous trichromatic test (AATT). A trained physician in community health service centre will invite the potential participants to undergo a physical examination and neurologic diagnosis of MCI. Participants who met the eligibility criteria will be assessed with a baseline assessment and then given the EEG evaluation in the 2 days preceding the start of the cognitive training.

After that, according to the random allocation sequence, participants will be randomly assigned to one of two groups with a targeted assignment ratio of 1:1. The random allocation sequence with a block size of four will be generated using a computer randomization list by an independent researcher assistant. The random allocation sequence is sealed in opaque envelopes by an assistant. The cognitive training group will receive cognitive intervention and health education, whereas the wait-list control group will only receive health education during the research period. During the 3 months follow up, the cognitive training group and wait-list control group will receive no interventions. Complete all outcome assessments, participants in the wait-list control group will be permitted to undergo the process-based multi-task cognitive training program. Although it was not initially the plan, the health education manual for mild cognitive impairment will be provided for participants who are not finishing the cognitive training or health education through various means, such as email, public platform, and short messaging service. All outcome measurements will be assessed at baseline, 10 weeks and 3 months follow up. Study assessments and timelines are illustrated in **Table 3**.

**Table 3 T3:** Summary of study assessments and timelines.

Time point	Measurement	Post-allocation					Mode of Administration
		Baseline	Training sessions	10 weeks assessments		Follow-up 3 months	
		T0		T1		T2	

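### The conditional listwise-deletion rule sits badly with the stated intention-to-treat analysis and can discard observed week-10 data

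*Protocol article*

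**What the plan says.** Statistical Considerations sets the principle: "The primary and secondary outcome measures were analyzed using data from the intention-to-treat". The same paragraph gives a two-branch rule for missing data. "Listwise deletion will be adopted to estimate treatment effects" applies "if missing values satisfy the criteria of the losing data entirely at random"; "otherwise, multiple imputation data strategies will be adopted". No test or criterion for choosing the branch is named. The paragraph also plans a comparison of completers with dropouts, a sensitivity analysis of completers, and a protocol set that requires at least 80% adherence and all assessments.

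For the primary outcome, "a repeated ANOVA test will be used to evaluate the differences of changes and long-term effect in outcome measurement index performance", with time and interaction effects. Study Procedure fixes the visits: "All outcome measurements will be assessed at baseline, 10 weeks and 3 months follow up". The sample-size paragraph under Study Design and Participants bases the calculation on "the change in executive function after 10-week, which is the primary outcome variable in this study" and allows for 15% dropout. The same section lists grounds for withdrawal: severe medical events, and "reluctant themselves in training at any time, and a major protocol violation".

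**The concern.** Under the first branch, the treatment effect is estimated in people with complete data, not in everyone randomised. Three things follow.

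- **The trigger is unsafe.** Missing completely at random is an assumption. Observed data can contradict it but cannot confirm it, and with so few dropouts even a clear departure can go unnoticed. The choice of primary method would then rest on a weak, data-dependent judgement.
- **Primary-endpoint data are discarded.** One ANOVA covers both the 10-week change and the later effect. Deleting incomplete cases across three visits removes people whose 10-week change was observed.
- **The back-up is not independent in this branch.** The completer sensitivity analysis makes the same exclusion as the main analysis, so it cannot reveal bias caused by that exclusion.

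At stake are the precision of the primary estimate and, if dropout relates to response, its validity.

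**Working it through.** **Inputs from the article.** Effect size 0.575, power 80%, type 1 error 5%, independent t-test, 78 evaluable, 15% dropout, 46 per group, 92 in total.

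**Step 1: reproduce the stated sample size.** Exact noncentral-t power with d = 0.575 and a one-sided 5% test gives 39 per arm, total 78, power 80.8%. A two-sided test needs 49 per arm, total 98. Inflating for dropout, 78 / (1 − 0.15) = 91.8, so 92. The stated 78 and 92 therefore reproduce, but only one-sided. Sidedness is a separate matter, so power is shown both ways below.

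**Step 2: expected losses.** 92 × 0.15 = 13.8 dropouts; 92 × 0.85 = 78.2 complete cases. The abstract's total of 90 would give 13.5 dropouts.

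**Step 3: observed week-10 data discarded.** Let f be the share of dropout that occurs after week 10. The article does not give f, so the whole range is shown. Listwise deletion keeps 78.2 people. Using every week-10 score keeps 92 − 13.8 × (1 − f).

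| f | Week-10 scores observed | Discarded by listwise deletion | One-sided power, all week-10 data | Two-sided power, all week-10 data |
|---|---|---|---|---|
| 0 | 78.2 | 0 | 80.9% | 70.9% |
| 1/3 | 82.8 | 4.6 | 82.9% | 73.4% |
| 1/2 | 85.1 | 6.9 | 83.8% | 74.6% |
| 2/3 | 87.4 | 9.2 | 84.6% | 75.7% |
| 1 | 92.0 | 13.8 | 86.3% | 77.9% |

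Listwise power is the f = 0 row throughout. The loss is zero if all dropout precedes week 10. From f = 1/3 upwards it runs from 82.9 − 80.9 = 2.0 points (one-sided) to 77.9 − 70.9 = 7.0 points (two-sided, f = 1).

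**Step 4: bias when dropout depends on response (illustration).** Assumptions not in the article: correlation 0.6 between visits; 15% dropout in each arm, all after week 10; in the training arm the log-odds of dropout rise as the observed week-10 change falls; the missingness check is a 5% t-test of week-10 change in dropouts against completers. The contrast is the planned one, the group difference in baseline-to-week-10 change, in outcome-SD units with true value 0.575.

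| Log-odds slope per SD of change | Check rejects | Listwise estimate when it does not reject | All observed week-10 data |
|---|---|---|---|
| 0 (completely at random) | 5% | 0.575 | 0.575 |
| 0.4 | 9% | 0.63 | 0.575 |
| 0.8 | 21% | 0.68 | 0.575 |
| 1.6 | 50% | 0.75 | 0.575 |

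If 0.575 is instead expressed in SDs of the change score, the last three listwise values become 0.63, 0.69 and 0.77.

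**Step 5: direction.** Now let training-arm dropout (about 19%) concentrate at low baseline, with 10% random dropout among controls. At log-odds slopes of 1.2 and 1.5, the completers' change contrast is 0.50 and 0.49, below the true 0.575. The sign of the bias depends on the dropout mechanism.

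**The case against.** The strongest reply is that the rule confines listwise deletion to the one condition in which it is unbiased and specifies imputation for every other case, so it does not flatly contradict intention-to-treat. It adds that losing about 14 people was already budgeted, since 78 is the evaluable target. Both statements are correct. Under true missing completely at random, Step 4 shows no bias and the cost is precision. What does not stand is that the condition can be verified, or that people with an observed primary outcome have to be among the losses.

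Three stronger readings are tempting but not supported.

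- **Withdrawals are concentrated in the training arm.** A reader might infer this because reluctance to train is a listed ground. The article lists the grounds for all participants, includes severe medical events, and gives no split by arm. Controls also attend twice-weekly classes. The arm-specific dropout in Steps 4 and 5 is an assumption.
- **A significance test triggers the rule.** None is named. The rejection rates belong to the check assumed here; another check would give others.
- **The primary effect would be inflated to about 0.70.** In the baseline-dependent scenario that figure arises from comparing completers' week-10 scores without baseline adjustment, which is not the planned analysis. The planned change contrast moves the other way, and a baseline-adjusted analysis of the same completers gives 0.57 to 0.58. That scenario shows the cost of omitting baseline, not of listwise deletion alone.

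**Conclusion.** The point holds in moderate form and should be fixed. The article fixes a rule under which the primary estimate may come from complete cases only, on a condition that the data cannot establish, and the three-visit model then discards some observed 10-week outcomes.

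The size depends on unknowns. Between 0 and about 14 people with week-10 data are lost, according to dropout timing. Under true missing completely at random this costs nothing if all dropout precedes week 10, and about 2 to 7 power points at d = 0.575 if a third or more comes later. Under the assumed response-dependent dropout, the retained listwise estimate is 0.63 to 0.75 against 0.575; other mechanisms push it below the truth. These values illustrate vulnerability and do not predict this trial's result. The conclusion also assumes that deletion is applied across all three visits, as the single repeated ANOVA implies.

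**What to change.** Delete the conditional rule. Make the primary analysis a likelihood-based mixed model on all randomised participants, using every available visit with baseline adjustment, and take the group contrast at week 10. This is valid under missing at random. Alternatively, use multiple imputation in every case. Report complete-case and protocol-set results as supportive only.

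Optional additions are a delta-adjusted sensitivity analysis for departures from missing at random, and a sentence saying whether outcome assessments are still sought after someone stops the programme.

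The cost is a rewording of the missing-data sentences and slightly more analysis work. The design, visits and sample size do not change.

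### The trial is sized on one week-10 change comparison, but the primary analysis is a three-visit repeated ANOVA with no deciding effect and with simple effects only after a significant interaction

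*Protocol article*

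**What the plan says.** The sample-size paragraph, under Study Design and Participants, fixes the target: "The calculation of sample size is based on the change in executive function after 10-week, which is the primary outcome variable in this study". It uses an independent t-test with effect size 0.575, 80% power and 5% type 1 error, and "the calculated total sample for this study is 78". The end of the Background makes the effect on executive function the primary aim and its maintenance over 3 months part of the secondary aim.

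Outcome Measurement defines the primary outcome as a composite z score measured at baseline, 10 weeks and 3 months, without naming a visit. Statistical Considerations then says that for the primary outcome "a repeated ANOVA test will be used to evaluate the differences of changes and long-term effect in outcome measurement index performance", and lists between-group, within-group and interaction effects. It adds: "The simple effect analysis will be added when there is an interaction between intervention factors and time factors". The 0.05 threshold applies to all comparisons.

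**The concern.** The sizing implies one test at one visit. The analysis offers three effects and does not say which decides the trial.

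- **Group main effect.** It averages the arm difference over all three visits. Study Procedure places the baseline assessment before randomisation, so one of the three carries no treatment effect.
- **Interaction.** With two arms and three visits it has 2 degrees of freedom. It does test whether change differs between arms, but it merges the primary week-10 question with the secondary maintenance question. A significant F does not say which visit differs.
- **Simple effects.** They are reached only through the interaction. If the simple effect is a between-arm comparison at week 10, it makes no use of the baseline score.

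At stake are the power to reach a week-10 conclusion and the freedom to choose the deciding effect after the data are seen.

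**Working it through.** **Inputs from the article:** d = 0.575, 39 evaluable per arm (78 in total), 15% dropout, 1:1 allocation, three visits.

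**Assumptions not in the article:** compound symmetry; visit correlation ρ of 0.5 to 0.7; share f of the effect kept at 3 months of 1, 0.5 or 0; two-sided 5%; d expressed in week-10 score SDs.

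**1. The article's own figure.** The noncentrality is d√(n/2) = 0.575 × √19.5 = 2.539 on 76 df. One-sided 5% gives 81% power at 39 per arm and just under 80% at 38, so 78 reproduces. Then 78/0.85 = 91.8, which rounds up to the stated 92. Two-sided 5% gives 71% at 39 per arm and would need 49 per arm. The sidedness is a separate matter. It explains why a two-sided t-test below starts at 71% rather than 80%.

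**2. Formulas, n = 39.** The arm differences at the three visits are δ = (0, d, f·d).

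- Change-score t-test: 2.539/√(2(1−ρ)), 76 df. This is 2.539 at ρ = 0.5 and 3.278 at ρ = 0.7.
- Baseline-adjusted week-10 contrast (ANCOVA): 2.539/√(1−ρ²), 75 df. This is 2.932 and 3.555.
- Interaction F: λ = (n/2)·Σ(δ − mean δ)²/(1−ρ), df 2 and 152. The sum of squares is 0.2204 for f = 1 or 0 and 0.1653 for f = 0.5. So λ = 8.60 or 6.45 at ρ = 0.5, and 14.33 or 10.75 at ρ = 0.7.
- Group main effect: mean δ·√(n/2)/√((1+2ρ)/3), 76 df. For f = 1 and ρ = 0.5 this is 0.3833 × 4.416/0.8165 = 2.073.
- Gated route (interaction P < 0.05, then a between-arm t-test at week 10): simulation, 40,000 runs per scenario.

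**3. Power, for f = 1 / 0.5 / 0 where it depends on f**

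| Test | ρ = 0.5 | ρ = 0.7 |
|---|---|---|
| Group main effect | 54 / 34 / 18% | 46 / 29 / 15% |
| Gated week-10 simple effect | 55 / 50 / 60% | 67 / 63 / 68% |
| Interaction F | 74 / 61 / 74% | 93 / 84 / 93% |
| Change-score t-test | 71% | 90% |
| Baseline-adjusted week-10 contrast | 82% | 94% |

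**4. If d is in change-score SDs instead.** The change t-test has 71%, the interaction 61–74%, and the adjusted contrast 75–88% (ρ from 0.8 down to 0.3).

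**5. No treatment effect (simulation, ρ = 0.5 and 0.7).** Interaction followed by a significant between-arm simple effect at week 10 or 3 months occurs in 1.1–1.7% of trials. Group or interaction significant occurs in about 10%; treating the two as independent gives 1 − 0.95² = 9.75%.

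**The case against.** The best defence is that the interaction is itself the test of differential change, and the week-10 change contrast lies within it. This stands. When the effect is fully kept or fully lost at 3 months, the interaction F slightly beats the change t-test (74% against 71% at ρ = 0.5, 93% against 90% at ρ = 0.7). It loses only when half is kept (61% against 71%, 84% against 90%). A reader might infer that the plan never tests the powered question, or always costs power. Neither follows.

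A reader might also infer that the plan doubles the type I error. The article nowhere says that either a group effect or an interaction counts as success. The figure of about 10% applies only under that rule, which the text leaves open but does not state. The sequence it does state is conservative.

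Three further points are fair. The sizing used change with a t-test, not ANCOVA, so the baseline-adjusted contrast is a recommendation and not something the plan departs from. The article does not say whether simple effects are by visit or within arm. And ρ, the persistence and the SD behind d are assumptions.

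Finally, an analysis plan that is not shown might name the primary contrast, and silence alone would be weak ground. But the article does state the method and its conditional path, and these do not match its own sizing target or its ordering of aims.

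**Conclusion.** The point holds as a mismatch between the sizing target and the stated primary analysis, with no rule for which effect decides the trial. It should be fixed, but it does not make the analysis invalid: repeated ANOVA is a valid method in a randomised trial.

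The cost depends on the route taken. It is large if the conclusion rests on the group effect or on a gated week-10 simple effect, and small or absent if it rests on the interaction F with full or no persistence. For ρ from 0.5 to 0.7, the adjusted week-10 contrast is the most powerful of the five tests in every scenario examined. Its lead over the interaction F ranges from about 1 point (ρ = 0.7, effect fully kept or lost) to about 22 points (ρ = 0.5, half kept). The direction is the same if d is in change-score SDs, with lower power. All of these figures rest on the stated assumptions about correlation, compound symmetry and persistence.

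**What to change.** In Statistical Considerations, name one primary test: the between-arm difference in the executive composite at week 10, adjusted for the baseline composite, tested at two-sided 5%. Estimate it by ANCOVA, or by a linear mixed model with baseline as covariate and arm, visit and arm-by-visit over week 10 and 3 months. Make the 3-month contrast from the same model secondary. Do not make either contrast conditional on the interaction.

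The data are already collected at the planned visits and the models run in the SPSS already named. The cost is a small change to the analysis wording, best made before outcomes are examined by arm.
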